**Fig. 1 Fig1:**
[figure not shown]
Flow chart of study design

### Eligibility criteria

The primary inclusion and exclusion criteria are listed in Box 1. In addition to these, all participants will be required to complete a standardised medical assessment with their general practitioner (GP) prior to entry in the study. Participants must return clearance form signed by the GP, confirming that they are medically fit to participate, and that the GP agrees to monitor the medical and psychiatric stability of the participant throughout the trial at intervals they deem to be clinically appropriate.

**Box 1 Tab1:** Eligibility criteria for participation in trial

*Inclusion criteria* Aged 16 years or older; Meets DSM-5 criteria for BN (purging or non-purging type) or Other Specified Feeding or Eating Disorder (OSFED) with bulimic behaviours i.e., must have engaged in objective binge episodes (OBEs) and inappropriate compensatory behaviours (vomiting, excessive laxative or diuretic use, extreme exercise or severe dietary restriction) at least once per week in the preceding 2 months; BMI of 20 or above; Access to a private space with sufficient technology to engage in telemedicine sessions (i.e., digital device with video camera and internet connection) *Exclusion criteria* Currently engaged in ongoing psychological treatment for their eating disorder; Non-proficient English speaker; Serious medical instability; Active suicidality or self-harm behaviours; Severe psychiatric conditions that would interfere with treatment (e.g., psychosis); Pregnant or breast-feeding; Current use of any stimulant medication; Reside outside of Australia	

### Interventions

#### Binge Eating eTherapy (BEeT)

All participants will receive access to BEeT, including both intervention conditions and WLC condition (post 10-week waitlist period). BEeT is an online self-help program that delivers the core components and strategies of CBT proven to be effective in treating eating disorders. BEeT is a 10-week program which consists of 10, one-hour interactive multimedia sessions. BEeT aims to decrease binge eating episodes and compensatory behaviours through the introduction of behavioural techniques which work to establish structured, regular eating patterns as well as cognitive techniques designed to challenge unhelpful thinking patterns related to one’s weight and appearance (See Table 1 for outline of the program components). Users are guided through the online sessions by pre-recorded videos of a therapist. Also included within the sessions are interactive activities to assist users in gaining a personalised understanding of key CBT skills. Each session becomes available every seven days, given that the previous session has been fully completed. Additionally, the program contains an inbuilt digital calendar to promote real-time self-monitoring practice via their digital device using tools such as food diary monitoring, thought challenging, feared foods exposure, and meal planning. The self-monitoring tools uphold several interactive features including a daily or weekly goal setting, scheduled reminders of goals or planned mealtimes, labelling of thoughts and emotions using animated text and images, reminders of coping skills practice, prompting questions to assist with re-framing thoughts, and a visual overview of weekly logs using colour coding to assist with recognising patterns in eating behaviours and thoughts.

**Table 1 Tab2:** Overview of binge eating etherapy session content

Session	Focus	Key principles
Session 1	Formulation and monitoring eating	Psychoeducation about cognitive-behavioural therapy Introduction to self-monitoring of eating behaviours
Session 2	Eating regularly and planning ahead	Development of personalised case formulation Psychoeducation about the role of restricting food and starvation Regular eating
Session 3	Addressing binges	Key strategies and skills to overcome binge eating and cope with urges to binge The role of triggers in the Binge Eating Cycle
Session 4	Problem solving and motivation	Problem solving Motivational enhancement strategies: pros and cons of change
Session 5	Understanding and noticing thoughts and feelings	Psychoeducation about emotions and unhelpful thinking patterns Emotion regulation skills Introduction to self-monitoring of unhelpful thoughts
Session 6	Coping with thoughts and feelings	Mid-treatment reflection upon strengths and progress Thought challenging
Session 7	Exposure challenges: Feared foods and food rules	Introduction to feared foods and food rules Development of personalised exposure hierarchy How to challenge feared foods and food rules using ‘Exposure Tool’
Session 8	Exposure challenges: Body image	Psychoeducation about body image Identification of exposure tasks to overcome checking and/or avoidance Urge surfing
Session 9	Self-compassion and identifying values and strengths	Strategies to foster greater self-compassion and body acceptance Identifying personal values and strengths external to eating, weight, and shape
Session 10	Review and relapse prevention	Relapse prevention strategies Reflection upon progress and changes in symptoms across treatment Discussion of other treatment options and support

#### Pure self-help BEeT

Participants allocated to the pure self-help BEeT treatment group will be given access to BEeT as described following after their baseline assessment.

#### Clinician-supported BEeT

Participants allocated to the clinician-supported BEeT treatment group will receive access to BEeT in addition to 10, weekly 30-min sessions with a support clinician delivered via a videoconferencing platform. The participant will be instructed to complete each weekly online BEeT session prior to attending the associated telemedicine support session.

The telemedicine sessions adopt the following structure:General check-in regarding participants’ wellbeing (e.g., mood, anxiety, sleep), their eating disorder symptoms (e.g., improved, worsened), and significant events that may have occurred since previous session.Review participants’ understanding of the content introduced in the previous online BEeT session.Review participants’ attempts to complete the learning tasks in their own time, with a particular focus upon debriefing the self-monitoring exercises.Review weekly weigh-in.Preparation for completion of the next online BEeT session.

All clinicians will have completed an online training course in how to deliver a supported self-help CBT intervention for BN, which outlines session by session what needs to be addressed in the support sessions. The clinicians will be existing staff of the service and may have various health qualifications, such as psychology, social work and dietetics. It is expected that participants will meet with their support clinician for a total of approximately five hours across the entire program.

#### Waitlist control

Participants in the WLC will be offered the pure self-help BEeT intervention after a waiting period of ten weeks (T1). During the waiting period they will complete 10, brief weekly psychological assessments (approx. 5 min in length) to monitor eating disorder symptoms, psychological distress and suicidal risk.

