### Trial design and setting

This study is a multisite, three-arm randomized controlled trial inclusive of two active interventions and a WLC. Participants will be recruited from the general community in Australia via advertisements on health websites and social media, referrals made from health professionals, and paper advertisements in mental health and medical clinics. If considered eligible following a screening call, the participant will be instructed to complete a standardised medical assessment with their general practitioner (GP) prior to entry to the study. After providing written informed consent, participants will be randomised to either the WLC condition or one of the intervention conditions, including pure self-help BEeT or clinician-supported BEeT. The intervention is entirely via digital modalities, including (1) *online eTherapy platform* and (2) *secure videoconferencing platform* (only for participants receiving clinician-supported BEeT). Participants randomised to the clinician-supported BEeT condition will engage in telemedicine sessions delivered by clinicians based at one of the following sites: specialist eating disorder outpatient clinic, adult community mental health team, university-based research team, and youth mental health clinic (headspace). All sites are based within New South Wales, Australia. See “Appendix A” for a list of study sites. Participants will be assessed at baseline (T0), weekly, post-intervention (T1: 12 weeks), and at 3-month follow-up (T2). The study commenced in May 2020. The study protocol has been approved by a Human Research Ethics Review Board (HREC #X18-0486). See Fig. 1 for an overview of the study process.

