## Outcomes

Data will be collected via online self-report assessments. Table 2 provides an overview of assessment points and outcome measures.

**Table 2 Tab3:** Schedule of enrolment, interventions, and assessments according to SPIRIT

	TIMEPOINT**	STUDY PERIOD						
		Enrolment	Allocation	Post-allocation				
		− T_1_	0	T_0_	Weekly monitoring	T_1_	T_2_	T_3_
**Enrolment**	Eligibility screen	X						
	GP Clearance	X						
	Informed consent	X						
	Allocation		X					
**Interventions**	Clinician-supported BEeT							
	Pure self-help BEeT							
	WLC							
**Assessments**	Demographics			X				
	General mental health			X				
	Self-harm and suicidality risk assessment			X	X	X	X	X
	Eating disorder examination questionnaire (EDE-Q)			X		X	X	X
	Eating disorder examination questionnaire-short (EDE-QS)				X			
	Kessler psychological distress scale (K10)			X	X	X	X	X
	Eating disorder quality of life questionnaire (EDQOL)			X		X	X	X
	Three-factor eating questionnaire (TFEQ)			X		X	X	X
	Young schema questionnaire			X		X	X	X
	Body mass index (BMI)			X	X^1^	X	X	X
	European quality of life-5 dimensions-5 levels (ED-5D-5L)			X		X	X	X
	Evaluation of external health services utilised			X		X	X	X
	Implementation surveys					X		
	Working alliance inventory-short revised (WAI-SR)^2^					X		
	Working alliance inventory for online interventions-short form (WAI-TECH-SF)					X		

**T_0_ = baseline assessment, T_1_ = 12 week assessment (post-intervention), T_3_ = 24 week assessment (3 month follow up), T_3_ = 36 week assessment (for WLC only)

^1^BMI measured in fourth week of participation. Also measured weekly from fifth to tenth week for participants where rapid weight loss is indicated

^2^Only administered to clinician-supported BEeT participants

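### The waitlist ends at ten weeks and that point is called T1, but T1 is set at 12 weeks with no exception for the waitlist arm

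*Protocol article*

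**What the plan says.** Two places give the wait as ten weeks. The description of BEeT under Interventions says that access is given to the "WLC condition (post 10-week waitlist period"). The Waitlist control section repeats the length and attaches the visit label to it: "Participants in the WLC will be offered the pure self-help BEeT intervention after a waiting period of ten weeks (T1"). It adds: "During the waiting period they will complete 10, brief weekly psychological assessments".

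Two other places put T1 at 12 weeks. Trial design and setting says: "Participants will be assessed at baseline (T0), weekly, post-intervention (T1: 12 weeks), and at 3-month follow-up (T2"). The Table 2 footnote under Outcomes has "T_1_ = 12 week assessment (post-intervention"), followed by "T_3_ = 24 week assessment (3 month follow up") and a 36-week visit that is the only one marked as specific to WLC. The footnote uses the label T3 for both the 24- and the 36-week visit. The first is evidently meant to be T2; this slip is separate and does not affect the point.

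The Primary outcome section takes binge frequency from the EDE-Q, which looks back over 28 days. On the release of sessions, the BEeT description says: "Each session becomes available every seven days, given that the previous session has been fully completed".

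**The concern.** T1 is the post-intervention assessment. Sample size bases the power calculation on change from before to after treatment, and Statistical methods compares the three arms on change in objective binge episodes. The T1 value in WLC therefore enters both BEeT-versus-WLC contrasts. The main economic hypothesis is also set at 12 weeks, and WLC is one of its comparators.

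Two dates for that visit leave two possible faults:

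- **WLC assessed at week 10, active arms at week 12.** Arm is then confounded with time since randomisation. The documents do not determine the direction of any bias.
- **BEeT opened to WLC at week 10, T1 held at week 12.** Part of the control arm's recall period may then follow access to the intervention. Any early benefit would shrink the difference between BEeT and WLC.

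The T1 comparison of clinician-supported with pure self-help BEeT is unaffected in either case.

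**Working it through.** No sample size, power or alpha enters here. The check sets the stated times side by side and does calendar arithmetic. It assumes that the ten-week and 12-week counts start on the same day (day 0) and that visits occur exactly on schedule.

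**Inputs**
- Wait: 10 weeks = day 70 (BEeT description; Waitlist control).
- T1: 12 weeks = day 84 (Trial design and setting; Table 2 footnote).
- Later visits: weeks 24 and 36 (Table 2 footnote).
- EDE-Q recall: 28 days (Primary outcome).
- Session release: seven days apart at the earliest (BEeT description).

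**1. Which wait fits the visit schedule?** The interval between 12-week T1 and the 24-week visit is 24 − 12 = 12 weeks. Allow WLC the same 12 weeks from access to post-treatment, and 12 more to follow-up:
- Access at week 12: 12 + 12 = 24 and 24 + 12 = 36. Both are scheduled visits.
- Access at week 10: 10 + 12 = 22 and 22 + 12 = 34. Neither is.

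The schedule therefore points to a 12-week wait.

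**2. WLC assessed at week 10.**
- WLC recall: 70 − 28 = 42, so days 42 to 70.
- Active-arm recall: 84 − 28 = 56, so days 56 to 84.
- Shared: days 56 to 70, that is 14 of 28 days (50%).

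**3. Access at week 10, T1 at week 12.** If a WLC participant starts *s* days after day 70, the recall days after the start number 84 − (70 + *s*) = 14 − *s*.

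| Start after access opens (*s*) | Recall days after start | Share of 28 |
|---|---|---|
| 0 days | 14 | 50% |
| 7 days | 7 | 25% |
| 14 days | 0 | 0% |

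Sessions could open on days 70, 77 and 84 at the earliest, so only sessions 1 and 2 could open before T1.

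**4. Access at a 12-week T1, after the EDE-Q.** No recall days follow access, and all arms are assessed at the same time.

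These are counts of calendar days. They do not convert into a bias in binge frequency, because the article gives no figure for the effect of the first two sessions.

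**The case against.** The strongest reply is that the Waitlist control section ties the offer of BEeT to T1 itself. Whichever week T1 is, access and assessment then coincide, and no control participant is exposed beforehand. Exposure arises only if a reader keeps the section's week number and drops its label. On the likely intent, a 12-week wait, the contrasts are sound and the defect is a wrong number in two sentences. This largely stands, and it is why the 50% can only be a hypothetical ceiling. It does not remove the conflict, since ten weeks and 12 weeks cannot both be T1.

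Fig. 1, to which the Participant timeline section refers, is not available here and may show the intent. The sentences would still disagree. T1 at 12 weeks may also allow slack to finish a ten-session programme, but that does not explain why week 10 is labelled T1.

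Even in the worst case, the session on addressing binges is the third and could not open before day 84. That limits the likely effect. It does not make it nil, because sessions 1 and 2 introduce self-monitoring and regular eating.

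Two stronger readings are tempting, and the documents support neither:

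- **That control participants have in fact used BEeT before T1, or that half of the control outcome is contaminated.** Nothing in the article shows what has been operated.
- **That ten weekly assessments leave WLC without risk monitoring for two weeks, against the Risk management section.** That section speaks of the duration of the trial, not of the wait. Table 2 schedules the risk assessment and the K10 at T1 as well as weekly. Nor is a gap in weeks 11 and 12 shown to be peculiar to WLC, since the active arms also have a ten-week programme before a 12-week T1.

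**Conclusion.** The inconsistency is real, lies in the current text, and concerns the date of the control arm's primary-outcome assessment. The discrepancy is two weeks. Its possible consequences are an assessment offset in which 14 of 28 recall days are shared, or between 0 and 14 recall days (0% to 50%) after access to BEeT. The second would bias the BEeT-versus-WLC contrasts towards no difference, so it would not manufacture a benefit. The size of either bias is unknown.

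The figures rest on a common day 0 for both counts and on visits held exactly on schedule; the 50% also needs access and use from day 70. A 12-week wait was probably intended, given the 24- and 36-week visits, and on that reading the analysis is unharmed once the text is corrected. The point is worth settling because the article as written permits a conduct that would affect two of the three between-arm contrasts.

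**What to change.** 1. Set T1 at week 12 from randomisation in all three arms. Change the ten-week wait to 12 weeks in both the Waitlist control section and the BEeT description.
2. State that BEeT opens to a WLC participant only once that participant's T1 EDE-Q is complete.
3. The article says: "The study commenced in May 2020". For WLC participants already enrolled, record the date of access and the date of T1. Keep the intention-to-treat analysis as primary. If any had access before T1, report how many and add a sensitivity analysis that accounts for assessment timing or exposure. Do not exclude them: that would remove people from one arm on the basis of an event after randomisation, and could remove most of the arm if ten weeks was the rule.
4. If weekly monitoring is run in weeks 11 and 12, make it the same in all arms. Adding it to WLC alone would create unequal monitoring just before the primary assessment in an unblinded, self-reported trial.

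The cost is a protocol amendment, a release setting on the platform and two recorded dates per WLC participant. The downside is that WLC participants may wait up to two more weeks. If ten weeks has been operated so far, the trial will contain two wait lengths, which the recorded dates will make visible.

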### Discontinuation criteria

Participants will be discontinued from the trial if a high level of medical or psychiatric risk is indicated. This includes severe mood instability requiring inpatient hospital admission (e.g., acute suicidality or deliberate self-harm), severe medical complications as confirmed by GP, or if the participant’s BMI drops below 19. Participants will also be discontinued if they are considered to have disengaged from the intervention evidenced by three weeks of non-completion of the online BEeT session or three consecutive missed telemedicine sessions (only for clinician-supported BEeT group).

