Several systematic reviews have concluded that digital self-help interventions are effective in reducing eating disorder behaviours [33–40]. There is evidence to also suggest that the treatment outcomes of self-help interventions are significantly enhanced by the addition of low-intensity support from a clinician, such as a fortnightly, check-in email or phone call [12, 39, 41–43]. Supported self-help interventions only demand one-fifth of the therapist contact hours required for a complete CBT course, meaning they can be delivered in settings with low resources and capacity limits [42]. The provision of clinician support as an adjunct to self-help programs has been suggested as a viable solution to one of the most powerful critiques of digital interventions, that being the high rates of non-adherence [37, 38]. Internet-delivered CBT has the highest dropout rates of all ED treatments, ranging up to 47.2% [44]. Given the potential impact of non-adherence upon the therapeutic outcomes for patients, several reviews have highlighted the need for ongoing development and examination of novel digital treatments, with the aim of reducing the discrepancy in adherence between online platforms and more traditional modes of face-to-face treatment delivery [35, 37, 38].

Two large published studies provide evidence for the use of online CBT-based, self-help programs for individuals with BN. As part of a randomised controlled trial (RCT) conducted by Sánchez-Ortiz et al. [45] significant improvements were reported in a sample of 75 patients with full or subthreshold BN following completion of an eight-session online CBT-based program. Abstinence rates were comparable to those of patients receiving a manual-based CBT self-help intervention and face-to-face CBT program [46, 47]. Similarly, Pretorius et al. [48] observed significant reductions in BN symptomology in response to an online CBT program, supplemented with email support from a clinician and peer support via message boards, which were maintained at six-month follow up. An abridged version of BEeT has also been successfully piloted proving its acceptability, feasibility, and effectiveness in reducing core symptoms of BN [49].

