### Adherence strategies

The BEeT platform contains in-built reminders to prompt engagement with the intervention. These include email notifications to alert participants to when a new online BEeT session is available and an automatic text message at approximately 6 p.m. to participants who have not made a food monitoring entry in the previous 24-h period. In addition, participants will be able to create their own personalised reminders specific to their weekly goals.

Additional efforts to re-engage participants in the pure self-help BEeT or WLC groups will consist of written contact via email to the participant after one week of disengagement, a phone call from researchers or clinicians after two weeks consecutive weeks of disengagement, and a letter to the participant and GP after three consecutive weeks of disengagement. The participant will be given an additional two weeks to reengage before they are discontinued from the trial.

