### Statistical methods

Initial exploratory analysis will be conducted to ensure baseline comparability between the two intervention groups and across sites. An intention to treat analysis will be conducted. Multiple imputation analysis will be implemented in accordance with missingness assumptions that fit the data (missing at random vs missing not at random), followed by a sensitivity analysis where appropriate. Generalised linear mixed modelling (GLMM) will be used to compare the effectiveness of pure self-help BEeT versus clinician-supported BEeT vs. WLC, collapsed across settings, using change in objective binge episode frequency as the primary outcome. Co-variates in the model will include baseline information of participant age, illness severity and length of illness. This will allow for assessment of the impact of participant characteristics on the key outcomes. Changes in secondary outcomes, such as psychological distress and quality of life, will also be analysed using a GLMM framework.

Time-to-event statistical methods, in particular survival analysis (cox proportional hazard modelling), will be used to examine non-compliance measures (e.g., time spent using intervention, dropout rates) and the factors impacting it (e.g., symptom severity, comorbid mental health difficulties). GLMM analysis will be used to consider the clinician-supported BEeT subgroup and factors impacting change in the EDE-Q, such as treatment setting and clinician experience to determine if the main outcome is affected by the setting in which treatment is delivered. Descriptive analysis will investigate the embeddedness and implementation of the treatment based on the clinician and the patient questionnaires.

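### Disengaged participants are removed from the trial under rules that differ by arm and are not reconciled, which puts the intention-to-treat estimate at risk of bias of unknown size and direction

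*Protocol article*

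**What the plan says.** Discontinuation criteria opens with safety grounds for leaving the trial and then adds disengagement: "Participants will also be discontinued if they are considered to have disengaged from the intervention evidenced by three weeks of non-completion" of the online session, or "three consecutive missed telemedicine sessions (only for clinician-supported BEeT group").

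Adherence strategies describes a contact sequence of email after one week, a phone call after two and a letter after three. It is introduced for two arms only: "Additional efforts to re-engage participants in the pure self-help BEeT or WLC groups will consist of written contact via email". The same paragraph ends: "The participant will be given an additional two weeks to reengage before they are discontinued from the trial".

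On the waitlist arm, Waitlist control says: "Participants in the WLC will be offered the pure self-help BEeT intervention after a waiting period of ten weeks (T1"). During the wait these participants complete ten brief weekly assessments and have no BEeT sessions.

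Statistical methods promises: "An intention to treat analysis will be conducted". On missing outcomes it says: "Multiple imputation analysis will be implemented in accordance with missingness assumptions that fit the data (missing at random vs missing not at random"), with a sensitivity analysis where appropriate. It also plans Cox modelling of non-compliance, naming dropout rates as one measure.

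**The concern.** An intention-to-treat analysis needs outcomes from participants whether or not they kept using the programme. A rule that takes people out of the trial because they stopped using it makes outcome loss a consequence of non-adherence. If the rule also works differently in each arm, the loss is no longer comparable between arms.

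Three things are at stake. The first aim compares supported BEeT with self-help BEeT and with the waitlist, so arm-dependent loss bears directly on the main contrasts. The Introduction presents non-adherence as a leading criticism of digital treatment ("Internet-delivered CBT has the highest dropout rates of all ED treatments, ranging up to 47.2" per cent), so the participants removed are the most informative ones on that question. In the dropout analysis, part of the dropout and its timing would be produced by the removal rule and not by participants' behaviour.

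The missing-data plan does not repair this. Whether data are missing at random (MAR) or not at random (MNAR) depends on values that were not observed. Fit to the observed data therefore cannot decide between the two.

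**Working it through.** **The rules side by side**

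| | Clinician-supported | Pure self-help | Waitlist, during the wait |
|---|---|---|---|
| Three weeks without an online session | applies | applies | no sessions to miss |
| Three missed telemedicine sessions | applies | does not apply | does not apply |
| Contact at one, two and three weeks | not stated | stated | stated |
| Two further weeks before removal | not stated | stated | stated |
| Time to removal | 3 weeks | 3 weeks, or 3 + 2 = 5 | start of disengagement undefined, then about 5 weeks |

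Either the two sections disagree on timing for the self-help arm, or removal is quicker in the supported arm than in the other two. On both readings the article is unclear on who leaves and when.

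**The plan's own sample size**

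Inputs from Sample size: three groups, f = 0.3, alpha 0.017, power 0.8. For a one-way ANOVA with 48 per arm, the noncentrality is N × f² = 144 × 0.09 = 12.96 and power is 0.803. The stated 48 is reproduced. The plan recruits 55 per arm for 16% dropout.

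Power on observed outcomes if loss differs from plan:
- 16% loss: 55 × 0.84 = 46.2 per arm, power 0.784.
- 47.2% loss: 55 × 0.528 = 29.0 per arm, power about 0.52.

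**Illustration of possible bias**

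The document gives no outcomes for non-adherers, so what follows rests on assumptions:
- Retained participants show the gap between the planning means, 23.7 − 14.9 = 8.8 episodes.
- Waitlist losses are random.
- Lost participants are imputed as if they were like retained ones, so the analysis returns 8.8.
- Loss p is 16% (planned dropout) or 47.2% (upper figure in the Introduction). Neither is a removal rate observed under this rule.
- Lost participants gain a fraction k of the effect.

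Effect in all randomised = 8.8 × [(1 − p) + p × k]. Relative error = 8.8 / that value − 1.

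| k | p = 16% | p = 47.2% |
|---|---|---|
| 0 | 8.8 × 0.840 = 7.4, overstated by 19% | 8.8 × 0.528 = 4.6, overstated by 89% |
| 0.5 | 8.8 × 0.920 = 8.1, overstated by 9% | 8.8 × 0.764 = 6.7, overstated by 31% |
| 1 | 8.8, no error | 8.8, no error |
| 1.5 (early improvers leave) | 8.8 × 1.080 = 9.5, understated by 7% | 8.8 × 1.236 = 10.9, understated by 19% |

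The sign depends on who leaves, and the document does not settle that.

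**The case against.** Several stronger readings are tempting, and the document does not support them.

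- **That BEeT's effect will be overstated.** A reader might infer this because non-adherers usually seem likely to gain less. The article gives no outcomes for them, and the sign reverses if early improvers are the ones who stop. Multiple imputation with an MNAR option is also planned. Upward bias is a risk, not a result.
- **That loss falls mainly on the active arms.** Adherence strategies names the waitlist group in the same removal procedure, and its weekly assessments could serve to judge disengagement. The missing definition is an ambiguity and does not show one-sided loss. In the supported arm the extra trigger overlaps with the session trigger, because each online session is meant to precede its support session.
- **That T1 and T2 data collection stops.** No section says so. Table 2 schedules these assessments without an adherence condition, and this is a condensed article. Still, removal from the trial with no mention of further follow-up makes loss the natural reading.
- **That the two sections flatly contradict each other.** They can be read together: three weeks identifies disengagement, and the contact steps and two extra weeks follow. That reading leaves the supported arm without a stated grace period.

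It is also fair to say that auxiliary variables and the details of a sensitivity analysis usually sit in an analysis plan, which is not shown. The criterion for choosing between MAR and MNAR, however, is stated in the article, and it cannot be applied.

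What stands is the removal rule as worded, its dependence on arm, the unreconciled timing and the unworkable imputation criterion.

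**Conclusion.** The concern holds as a risk of bias of unknown size and direction. Followed as written, the article removes participants from the trial for non-adherence, under rules that differ by arm, and provides for no outcome collection afterwards. That is at odds with the intention-to-treat commitment and distorts the planned dropout analysis.

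Under the stated assumptions, the error runs from 7% understatement to 19% overstatement at 16% loss, and from 19% understatement to 89% overstatement at 47.2% loss. The upper ends require that removed participants gain nothing and that imputation credits them with the full effect. These are illustrations and not estimates for this trial. The case for change does not depend on the sign: outcomes that were never collected cannot be recovered by analysis.

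**What to change.** 1. Separate disengagement from the programme from leaving follow-up. State that the T1 and T2 online questionnaires are sought from every randomised participant who has not withdrawn consent, and that the answers are analysed as randomised.
2. Replace the choice of missingness assumption by fit with a primary assumption set in advance, for example MAR imputation by arm using the weekly EDE-QS. Add a delta-adjusted MNAR sensitivity analysis that is always run. MAR is easier to defend once outcomes from disengaged participants are in the data, and the delta analysis shows how far the result depends on it.
3. Reconcile Discontinuation criteria with Adherence strategies for all three arms, covering the time to removal, whether the further two weeks apply in the supported arm, and what disengagement means during the waitlist period. Which rule to adopt is for the sponsor to decide.

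The cost is protocol wording, some extra questionnaire invitations and one more sensitivity analysis. Assessments are already online self-report, so the added burden is small. The estimated effect may turn out smaller.
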